### **c. Inclusion Criteria**

A patient will be eligible for study participation if he/she meets all the following criteria:

- All AIS patients treated with underarm (Boston) bracing who are ready to undergo brace weaning
- Primary curve ranging between 20 and 40 degrees of Cobb angle measurement

- Have reached skeletal maturity based on the Scoliosis Research Society (SRS) standardized criteria: Risser stage  $\geq 4$ ,  $>2$  years post-menarche, and no growth between 2 visits.

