## **Supplementary 2 Statistical Plan**

### **TITLE: A RANDOMIZED CONTROLLED TRIAL COMPARING GRADUAL AND IMMEDIATE BRACE WEANING FOR CLINICAL MANAGEMENT OF ADOLESCENT IDIOPATHIC SCOLIOSIS PATIENTS**

#### **DATA PROCESSING AND ANALYSIS**

##### **1. SAMPLE SIZE CALCULATION**

The sample size of this clinical trial will be determined based on an independent sample *t*-test to detect a difference between the two groups (immediate and gradual bracing weaning) for the changes in Cobb angle. According to a previous study [1], the average increase in Cobb angle at 1 year after brace weaning was 3.5 degrees. Curve progression is observed in 43.5% of patients. At 2 years, the curve progression rate was 46.5% with an average increase of major curve Cobb angle of 5.1 degrees. Based on this result, we consider a difference of 2 degrees between the changes in Cobb angle as clinically relevant, with an equivalence margin of 0.4. Assuming a standard deviation of 6 degrees for the Cobb angle change, a sample of 128 per group is required to detect the difference of the statistical test with 80% power at a 0.05 level of significance. Accounting for 20% overall attrition rate at 1 year follow-up, we will recruit 308 AIS patients (154 in each group) for this prospective study.

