##### **2. STUDY OUTCOMES**

Primary outcome was the change in major curve Cobb angle from baseline to 6-month, 12-month, and 24-month follow-up. Curve progression was examined as  $>5^\circ$  increase of major Cobb angle between follow-up time points and baseline. Secondary outcomes were the change in truncal balance in truncal shift and listing (C7-central sacral vertebral line deviation) from baseline to 6-month, 12-month and 24-month follow-up.

Secondary outcomes also included the refined Scoliosis Research Society 22-item (SRS-22r) questionnaire total score, the EuroQol-5-dimension (EQ-5D) utility score and EuroQol-visual analogue scale (EQ-VAS) at all post-weaning time points.

All study outcome measures were studied at baseline (the time of weaning), post-weaning 6, 12 and 24 months.

Body weight, standing and sitting body height, arm span, and HRQoL measures were measured, and curve type (i.e. thoracic, thoracolumbar/ lumbar) and coronal Cobb angle were assessed from whole spine standing posteroanterior and lateral radiographs taken simultaneously at each visit as per clinical routine. Skeletal maturity was routinely determined at the time of weaning using Risser staging, distal radius and ulna (DRU) classification and Sanders staging. In addition to Cobb angle and truncanl balance, other radiological parameters including T1 tilt, shoulder height, sagittal vertical axis (SVA), thoracic kyphosis (T5-12) and lumbar lordosis (L1-S1) were measured by two assessors independently. An intra-class correlation coefficient (ICC) with 95% confidence interval will be used to estimate the inter-assessor reliability.

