### **3. SUBGROUP ANALYSES**

In subgroup analysis, number of patients with curve progression since brace weaning ( $>5^\circ$  increase of major Cobb angle) at post-weaning 24 months in the PP population will be reported with percentages. Multivariable logistic regressions were used to examine specifically whether brace weaning protocol (immediate/gradual), skeletal maturity status at weaning (Risser staging, DRU grades and Sanders stages) and any significant baseline parameters were associating factors for curve progression.

Pearson's Chi-square test was used to compare the occurrence of progression/non-progression/rebound (with  $>5^\circ$  increase of major Cobb angle at follow-up but major Cobb angle at weaning was less than prebrace major Cobb angle) between weaning protocol.

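### The progression regression examines skeletal maturity through three overlapping scales with no single or joint test, and admits other predictors because they are significant in the same data

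*Supplement*

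**What the plan says.** The Subgroup Analyses section of the SAP defines progression as a rise of more than 5 degrees in the major Cobb angle. It reports counts at 24 months in the per-protocol population, and then fits logistic regressions (in the plural) to see whether weaning protocol, "skeletal maturity status at weaning (Risser staging, DRU grades and Sanders stages) and any significant baseline parameters were associating factors for curve progression".

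The Study Outcomes section of the SAP confirms that all three scales are available for each patient: "Skeletal maturity was routinely determined at the time of weaning using Risser staging, distal radius and ulna (DRU) classification and Sanders staging". The protocol's inclusion criteria require that patients "Have reached skeletal maturity based on the Scoliosis Research Society (SRS) standardized criteria: Risser stage" 4 or above, so all three scales are read in a group already selected as mature.

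The section does not say whether the scales enter one model or three, how they are coded, which of them decides the maturity question, which baseline variables are candidates, or what threshold makes one significant. It names no alpha; the SAP's only level is in the sample-size paragraph ("with 80% power at a 0.05 level of significance"). The only multiplicity correction is the Bonferroni adjustment of between-group comparisons in the ANCOVA under Secondary Analyses.

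**The concern.** Two features of the rule raise the chance of a wrong statement about who progresses.

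- **One question, several tests.** Risser, DRU and Sanders are readings of the same construct. In separate models, maturity gets three chances to be significant. In one model, each coefficient tests only what that scale adds beyond the other two, so all three can be non-significant although maturity matters.
- **Selection and testing on the same data.** A baseline variable enters because it is significant and is then reported as a factor from the same patients. Without a fixed list, the number of chances is unknown.

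This is the SAP's only analysis of which patients progress after weaning, and maturity is what the protocol uses to judge readiness to wean. A spurious or missed maturity factor could therefore colour how the trial is read.

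**Working it through.** The plan states no power, alpha or sample size for this regression, so there is no figure of its own to reproduce. The figures below size the problem.

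**Inputs from the SAP sample-size section.** 308 recruited; 20% attrition at 1 year; 46.5% progression at 2 years; level 0.05.
- 308 × 0.8 = 246 patients, and 246 × 0.465 = 114 events.
- Losses by 24 months and per-protocol exclusions are not given, so 200 patients (93 events) is used as a lower case.

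**Assumptions.** Level 0.05, two-sided, for this model; pairwise scale correlation r; odds ratio per SD; number and correlation of candidate variables. The documents give none of these.

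**1. False maturity finding.** For k independent tests the chance of at least one false positive is 1 − 0.95^k. For k = 3 this is 1 − 0.857 = 0.143. Simulation with correlated scales (n = 200-246, joint or separate models) gives about 8-15%. One 3-df likelihood-ratio test gives about 4-6%.

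**2. False factor of any kind.** The protocol's Study Measurements section and the SAP's Study Outcomes section name about 25 baseline items beyond the three scales: 6 demographic, 5 body size and menarche, 12 curve and balance, 2 brace history. The SAP describes a similar pool for the ANCOVA covariates; that it also serves this regression is an inference.
- Independent tests: k = 10 gives 0.40, k = 14 gives 0.51, k = 20 gives 0.64, k = 25 gives 0.72.
- Simulated screen at 0.05, then a fit with arm and three scales, all effects null:

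| Candidates | Assumed correlation | At least one false factor |
|---|---|---|
| 10 | 0 | 44-46% |
| 10 | 0.3 | 37% |
| 20 | 0 | 63-65% |
| 20 | 0.3 | 43-45% |
| 20 | 0.5 | 29-33% |
| 25 | in blocks: 0.7 (body size; age, grade and menarche), 0.2 (radiographic) | 61-63% |
| 25 | in blocks: 0.85 and 0.4 | 52-53% |

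Other runs with candidates correlated at 0.5 gave 25-30%. The final fit does little to remove chance findings: with independent candidates, 83-90% of null variables that pass the screen stay significant.

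**3. Missed maturity effect, all three scales in one model.** Let a shared driver act with log odds β = ln 1.65 = 0.501 per SD, and let each scale correlate √r with it.
- Variance inflation: VIF = 1/(1 − 2r²/(1 + r)), i.e. 1.16, 1.50 and 2.36 for r = 0.3, 0.5 and 0.7.
- Coefficient per scale: b = β√r/(1 + 2r). Power ≈ Φ(b·√(N·p(1 − p)/VIF) − 1.96), with p(1 − p) = 0.465 × 0.535 = 0.2488.
- N = 200, r = 0.5: b = 0.501 × 0.707/2 = 0.177; z = 0.177 × √(49.8/1.5) = 1.02; power Φ(−0.94) = 0.17.
- For r = 0.3 to 0.7 the formula gives 0.20 to 0.12 at N = 200 and 0.24 to 0.14 at N = 246. Simulation gives about 10-25%.
- Joint 3-df test: noncentrality N·p(1 − p)·β²·3r/(1 + 2r). For N = 200, r = 0.5 this is 49.8 × 0.251 × 0.75 = 9.4, power about 0.73. The formula spans 0.59 (N = 200, r = 0.3) to 0.88 (N = 246, r = 0.7). It treats the scales as continuous and is slightly optimistic; the simulated range is about 46-87%.

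**4. When the loss does not arise.** With each scale in its own model, at least one is significant in 67-96% under the same effect. If one scale alone drives progression (joint model, N = 246), power for that scale is:

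| OR per SD | r = 0.3 | 0.5 | 0.7 | 0.9 |
|---|---|---|---|---|
| 1.5 | 0.79 | 0.70 | 0.51 | 0.24 |
| 2.0 | 1.00 | 0.98 | 0.92 | 0.52 |

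**The case against.** The best case against acting has four parts.

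- **Standing of the analysis.** It comes after the primary and secondary analyses, no study aim or hypothesis concerns predictors, and the wording is that of association. Multiplicity control is not usually demanded at this level. This is right as to weight, and it limits the point to statements about factors. It does not remove the point: the section states a rule for admitting predictors and does not call the results exploratory. A subgroup heading does not do that work.
- **Power.** A reader might infer that a real maturity effect will mostly be missed. The documents do not support that. The plural leaves separate models open, and there the loss vanishes. In a joint model it depends on a shared driver, high correlation or a small effect, none of which the documents give. Restriction to Risser 4 or above probably lowers the correlations. At low correlation the joint test gains little over any-of-three: with a shared driver, OR 1.5, r = 0.3 and N = 246, it is 0.50 against 0.45.
- **False factors.** A reader might infer that they are more likely than not. That needs about 14 independent tests, or a pool like the 25 listed items with modest correlation. The SAP gives no count for this model, and related measures such as standing height, sitting height and arm span lower the figure.
- **Alpha.** That every term is tested at an unadjusted 0.05 is the natural reading, but it is an inference from the sample-size paragraph.

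**Conclusion.** The point holds in a bounded form. As written, the regression can err in two directions.

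- **Falsely positive:** about 8-15% for at least one maturity scale, and roughly 25-65% for at least one factor of any kind with 10-25 null candidates. Both rest on a level of 0.05; the second also rests on assumed counts and correlations. Every case examined is clearly above 5%.
- **Falsely negative:** possible, not established. It needs all three scales in one model together with a shared driver, high correlation or a small effect.

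The primary t-test and the ANCOVA are untouched. The change is worth making because the rule is explicit, the better alternative is simple, and the scales are already collected.

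**What to change.** In the Subgroup Analyses section of the SAP:

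1. Test maturity once. Either name one scale in advance, or use one likelihood-ratio test of Risser, DRU and Sanders together, and read individual scales only if that test is significant. Under a shared driver (OR 1.5, N = 246), the joint test does better when the scales are weakly correlated (0.50 against 0.39 at r = 0.3), and a single scale does slightly better when they are strongly correlated (0.74 against 0.70 at r = 0.7). State the coding of each scale.
2. Replace the clause admitting whatever baseline variables prove significant with a short list fixed before the treatment code is broken, for example weaning protocol, baseline major Cobb angle and curve type. Keep every listed term whatever its p-value.
3. Report any other predictor as exploratory, with odds ratio and 95% confidence interval and no claim attached.

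The cost is wording only; no new data are needed. The downside is that predictors outside the list become hypothesis-generating only.
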